## Abstract

**Background:**

Acupuncture is well recognized for its unique therapeutic effect for many diseases as a nonpharmacological therapy in traditional Chinese medicine (TCM). However, whether acupuncture can effectively treat fibromyalgia is currently unclear. Therefore, we aim to design a study protocol of a randomized controlled clinical trial and assess the effectiveness of acupuncture for patients with fibromyalgia, which may lead to alleviation of clinical symptoms and improvement of patients’ quality of life.

**Methods:**

The study is designed as a randomized, blinded, placebo-controlled trial of two cohorts conducted at Guang’anmen Hospital of China Academy of Chinese Medical Sciences and Shenzhen Traditional Chinese Medicine Hospital, respectively. A total of 68 patients with primary fibromyalgia, diagnosed with the American College of Rheumatology criteria, are randomly allocated with a 1:1 ratio to acupuncture or sham acupuncture groups. All subjects will receive acupuncture intervention for 8 weeks with follow-up assessments every 4 weeks for 16 weeks. The primary outcome will be evaluated using the visual analogue scale (VAS) and revised fibromyalgia impact questionnaire (FIQR) for pain intensity. The secondary outcome measures will include: Multidimensional Assessment of Fatigue scale (MAF), Short Form-36 (SF-36), Beck Depression Inventory (BDI), Pittsburgh Sleep Quality Index (PSQI), Chinese perceived stress scales (pss-14), changes in the number of 18 tender points, patient satisfaction for the treatment and adverse events. The mentioned outcome measurements will be assessed every 4 weeks for 6 months.

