### Outcome measurements

#### Primary outcomes

The visual analogue scale (VAS) [18] for pain intensity: Using a horizontal ruler of 100 mm, “0” representing no pain and “100” representing unbearable pain. The pain VAS intensity will be measured at the baseline, week 4, week 8. A total of seven assessments will be measured monthly during the 8-week treatment period and the follow-up period at week 12, 16, 20, and 24.Revised Fibromyalgia Impact Questionnaire (FIQR) [19] for pain intensity: FIQR assesses the health status of patients with fibromyalgia, including physical function, working condition, depression, anxiety, pain, stiffness, fatigue, sensitivity, and well-being. The scoring system ranges from 0 to 100, in which a higher score represents a heavier state of FM. Each subject will be asked to complete the questionnaire before treatment based on the overall situation of the past 24 h [20].

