
Adverse events will be monitored during the 8 weeks of treatment. Any adverse reactions occurred during the study will be documented in the “Adverse Reaction Form” while the patients are followed up until the symptoms disappear or the abnormal indicators return to normal. In the event of a serious adverse event, the necessary measures will be taken immediately for the safety of the subject.

Primary and secondary efficacy indicators will be evaluated every 4 weeks except the PGIC assessed after 8 weeks of treatment. Safety evaluations will be conducted at baseline and week 8 including blood pressure, breathing, heart rate, blood routine, urine routine, liver, and kidney function (ALT, AST, Cr, BUN), Electrocardiogram (Figs. 3 and 4).

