**Fig. 3 Fig3:**
[figure not shown]
Trial flow and study design. General information = name, gender, age, height, weight, duration of illness, smoking history, drinking history, education, job, family income. 1st outcome = pain-VAS, Revised Fibromyalgia Impact Questionnaire (FIQR). 2nd outcome = Multidimensional Assessment of Fatigue scale (MAF), SF-36, pss-14, Beck Depression Inventory (BDI), Pittsburgh Sleep Quality Index (PSQI), changes in the number of 18 tender points. 3rd outcome = Patient satisfaction for the treatment (PGIC)

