### Sample size

The calculation for sample size was based on the changes in pain VAS scores. We adopted the method described in previous studies [28, 29] that the changes are − 4.00 in the acupuncture group and − 2.50 in the sham-acupuncture group, respectively, indicating that the mean difference between two group is 1.5 with standard deviations of 2.55 and 1.25. Given that the ratio of the acupuncture group and the control group is 1:1, the required sample size is 29 cases for each group as estimated by SAS 9.4 software using a two-sided test with a significance level (α) of 0.05 and a power (1-β) of 0.80. With a possible dropout rate of around 15%, the acupuncture group and control group require a total of 68 cases.

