### Statistical analysis

For statistical analysis, mean ± standard deviation (M ± SD) is used for continuous variables which meet normal distribution. Chi-square or Fisher’s exact test will be performed to compare baseline characteristics for categorical variables. The primary outcome variable between the two groups will be analyzed by Chi-square test or Fisher’s exact test, while the analysis of independent-samples *t* test or Wilcoxon rank-sum test will be used for secondary outcomes.

To assess the effect of acupuncture therapy for fibromyalgia, intention-to-treat (ITT) [30] analysis will be performed for statistical analysis. A value of *P* < 0.05 with two-tailed test will be considered statistically significant.

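### Pain VAS and FIQR are both primary at six post-baseline visits, with no primary visit and no success rule beyond P < 0.05, while the sample size supports one VAS comparison only

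*Protocol article*

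**What the plan says.** Two outcomes share primary status. The abstract says "The primary outcome will be evaluated using the visual analogue scale (VAS) and revised fibromyalgia impact questionnaire (FIQR) for pain intensity", the Primary outcomes section lists both, and the Fig. 3 legend reads "1st outcome = pain-VAS, Revised Fibromyalgia Impact Questionnaire (FIQR" with no ranking.

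For VAS, the Primary outcomes section says "The pain VAS intensity will be measured at the baseline, week 4, week 8" and then "A total of seven assessments will be measured monthly during the 8-week treatment period and the follow-up period at week 12, 16, 20, and 24". That is baseline plus six later visits. The FIQR paragraph in that section mentions only completion before treatment, but the end of the outcomes section puts FIQR on the same schedule: "Primary and secondary efficacy indicators will be evaluated every 4 weeks except the PGIC assessed after 8 weeks of treatment". The abstract also has the outcomes assessed every 4 weeks for 6 months.

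The Sample size section says "The calculation for sample size was based on the changes in pain VAS scores". It names no visit and gives no FIQR difference or standard deviation.

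The Statistical analysis section refers to one primary outcome variable, assigns it a Chi-square or Fisher's exact test, and gives one decision rule for all analyses: P < 0.05 "with two-tailed test will be considered statistically significant". No section names a primary visit, an order of testing, a split of alpha, or whether one or both outcomes must succeed.

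The article attaches the label of pain intensity to FIQR, yet its own description is a 0–100 health-status score that also covers function, work, mood, stiffness and fatigue.

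**The concern.** The primary endpoint, its time point and the criterion for success define the hypothesis that the sample size is meant to serve. Here two outcomes and six visits give up to 12 candidate primary comparisons, and the text allows a claim of success on any of them at the full 5% level. The Background and Discussion describe the existing evidence as conflicting, so a positive result picked from 12 would be hard to interpret.

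The opposite reading, that both outcomes must succeed, protects against false positives. But the trial was not sized for it.

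**Working it through.** **1. Reproduce the plan's sample size.** Inputs from the Sample size section: difference 1.5, SDs 2.55 and 1.25, two-sided α = 0.05, power 0.80, ratio 1:1, dropout about 15%.

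- Pooled SD = √((2.55² + 1.25²)/2) = 2.008.
- n per group = 2 × [2.008 × (1.960 + 0.842)/1.5]² = 28.1, rounded up to 29. This matches the plan. Power at 29 is 0.81 by the normal formula and 0.80 by the t test.
- Dropout: 29 × 1.15 = 33.4, so 34 per group and 68 in total. Dividing instead, 58/0.85 = 68.2, so 69. The stated 68 is reproduced closely enough.

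This calculation covers one VAS comparison at full alpha and nothing more.

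**2. Count the candidate tests.** 2 outcomes × 6 visits (weeks 4, 8, 12, 16, 20, 24) = 12.

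**3. Chance of at least one false-positive primary result.** If the tests are independent, this is 1 − 0.95^k: 9.75% for k = 2, 26.5% for k = 6, 46.0% for k = 12. The article gives no correlations, so 0.3 to 0.9 is assumed both between outcomes and between visits. Correlated normal test statistics were simulated under no effect (400,000 draws, two-sided 0.05, visits either equally correlated or with correlation decaying over time).

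| Reading | Assumed correlations | False-positive chance |
|---|---|---|
| Any outcome, any visit (12 tests) | both 0.3 | 42–44% |
| | both 0.7 | 26–31% |
| | both 0.9 | 15–18% |
| One fixed visit, either outcome | 0.3 to 0.9 (or independent) | 9.5% down to 7.1% (9.75%) |
| One fixed visit, both required | any | at most 5% |

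**4. The tests the plan actually names.** Chi-square and Fisher need dichotomised scores, and the article gives no cut-off. Assumptions: responder rates of 30% and 50%, 29 or 34 analysed per group, correlations of the underlying scores 0.3–0.7 between outcomes and 0.3–0.8 between visits.

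- Fisher: about 19–27% for 12 tests (about 18% at the lowest, with 29 per group), and about 5% for two outcomes at one visit, because the exact test is conservative at this size.
- Chi-square: about 29–47% and 8–11% respectively.

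**5. Power if both must succeed.** P(both succeed) ≤ P(VAS succeeds), so joint power cannot exceed about 0.80. Nothing tighter follows, because FIQR has no stated effect or SD.

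**6. Cost of splitting alpha between the two outcomes at one visit (0.025 each).** n = 2 × [2.008 × (2.241 + 0.842)/1.5]² = 34.1, so 35 per group. With dropout, 35/0.85 = 41.2, so 42 per group. At 29 per group the power for VAS would be 0.73.

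**The case against.** A reader might infer that the trial's false-positive rate is several times 5%. The documents do not support that as a flat statement. They give a measurement schedule, not a list of 12 tests, and the Statistical analysis section speaks of a primary outcome variable in the singular. With one visit fixed, the error is under twice nominal for either outcome, about nominal with Fisher's test, and at most 5% if both are required. The size must therefore be stated conditionally.

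A reader might also put a figure on joint power by giving FIQR 80% power as well. The article has no FIQR input, so only the upper bound stands. Nor does the pain-intensity label show that an FIQR result would be reported as pain relief. It is a wording fault to correct.

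The strongest defence is that this is a condensed article, and rules for alpha and for combining outcomes often sit in an analysis plan that is not shown. Some features also point to week 8: treatment ends then, PGIC is taken then, and weeks 12–24 are called follow-up. This lowers the certainty about what will be done, but it does not remove the point. The article never names week 8 as primary. It states two unranked primaries, one threshold, and a sample size that fits only one comparison. That is a poorly fixed endpoint, not an omitted detail. Basing the sample size on VAS does not make VAS the sole primary outcome, because FIQR is still listed beside it.

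**Conclusion.** The point holds in conditional form. As written, success could be claimed on either outcome at any visit. On that reading the chance of a false-positive primary result is about 15–44% with normal-theory tests (46% under independence), and about 19–27% with Fisher's test. Fixing the visit alone brings it to about 7–10% (about 5% with Fisher). Requiring both outcomes holds it to 5% or less, but with unknown power no higher than that for VAS. The ranges rest on assumed correlations and, for Fisher, assumed responder rates. The absence of a primary visit and of a success rule rests on the text alone.

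**What to change.** Before unblinding, amend the protocol, analysis plan and registry entry as follows.

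- Name one primary endpoint: change in pain VAS from baseline to week 8. It uses the sample-size variable at the end of treatment.
- Test it at two-sided 0.05 by a comparison of means, for example adjusted for baseline. This must replace the Chi-square or Fisher test assigned to the primary outcome, which cannot test a mean change.
- Make FIQR total at week 8 the key secondary outcome, tested at 0.05 only if VAS is significant.
- Report weeks 4 and 12–24 as supportive estimates with confidence intervals.
- Describe FIQR as overall fibromyalgia impact, not pain intensity, and bring its assessment times in the Primary outcomes section into line with the 4-weekly schedule.

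Requiring both outcomes, or splitting alpha, is also valid if power is restated. The split would need 35 per group before dropout.

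The recommended route changes wording only and keeps the sample-size basis. Its small downside is that FIQR can no longer succeed on its own.

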**Discussion:**

This clinical trial will use advanced research methods to evaluate the efficacy and safety of acupuncture on fibromyalgia. The results of this trial may provide clinical evidence on the beneficial effects of acupuncture in treating fibromyalgia.

**Trial registration:**

Chinese Clinical Trial Registry, ChiCTR1800016826: AMCTR-IOR-18000184. Registered 27 June 2018, http://www.acmctr.org/listbycreater.aspx

## Background

Primary fibromyalgia (FM) is a chronic clinical condition characterized by diffuse pain and stiffness as the major clinical feature, which is often accompanied by fatigue, weakness, sleep disorders, emotional abnormalities, and cognitive dysfunction [1]. The prevalence of FM is about 2–8% with the male-to-female ratio of about 1:9 [2, 3]. The clinical manifestations of FM are complex and diverse, including persistent pain, fatigue, and sleep disorders [4].

Although the etiology of FM remains unclear, it is currently considered that both neuroendocrine changes and immune dysregulations are involved in the pathogenesis of this disease [3]. Current treatments of FM mainly include pharmacotherapy and nonpharmacologic therapy. Antidepressants are the choice of medication for the treatment of FM, among which the tricyclic antidepressant amitriptyline is the most widely used. The second-generation anticonvulsant pregabalin is the first drug approved by the FDA for the treatment of FM. Other therapeutics including reuptake inhibitors, highly selective monoamine oxidase inhibitors, and analgesics. Non-opioid central analgesic tramadol has also shown certain effects in treating FM [5]. However, the overall therapeutic effects of the above drugs are considered to be less than satisfactory since only a small portion of patients could receive the expected benefits [6]. Currently, the available treatments in traditional Chinese medicine (TCM) comprise diverse and effective nonpharmacologic therapies such as acupuncture, massage, cupping, tai chi, and qi gong. Notably, the newly revised FM treatment recommendations by EULAR have placed acupuncture as one of the specific recommendations for the nonpharmacologic therapies since acupuncture has been shown to alleviate pain, relieve fatigue, and improve the quality of life in patients with FM [7].

Acupuncture has been used in medical practice with little side effects and low cost for more than 2000 years in China and is now widely recognized around the world. Based on the meridian theory, acupuncture therapy could promote flow of qi and blood circulation and regulate the balance of Yin and Yang, which has been used in the treatment of many diseases and clinical syndromes. A large number of studies have demonstrated the efficacy and advantages of acupuncture therapy in alleviating chronic pain [8], insomnia [9], anxiety, and depression [10]. Acupuncture exhibits a rapid pain-relieving effect for the chronic soft tissue diseases, which has been confirmed by research findings on its anti-inflammatory and analgesic effects and improvement of microcirculation [11, 12]. Although acupuncture has shown certain efficacy and safety in treating FM cases, several studies have also reported no significant difference between acupuncture therapy and placebo treatment [13–15].

Thus, this study aims to provide a protocol for clinical trials with randomized controlled studies to confirm the therapeutic effects of acupuncture in the treatment of FM.

## Methods

### Study design

This study is a two-center, blinding, randomized, controlled trial with two arms for 8 weeks. A total number of 68 patients with FM who meet the criteria are randomly divided into acupuncture group and sham acupuncture group according to the ratio of 1:1. The intervention will be performed for 8 weeks with a follow-up of 16 weeks. The treatment of acupuncture and placebo is three times a week for the first 4 weeks and twice a week for the next 4 weeks. This clinical trial will be completed at Guang’anmen Hospital of China Academy of Chinese Medical Sciences and Shenzhen Traditional Chinese Medicine Hospital. This study will follow the relevant regulations of the World Medical Congress “Helsinki Declaration” and has been approved by the Ethics Committee of Guang’anmen Hospital and Shenzhen Traditional Chinese Medicine Hospital. All enrolled subjects will be informed with a complete and comprehensive introduction including the purpose, procedure, and possible risks of the study. The informed consent will be obtained before the start of this study.

### Participants

#### Inclusion criteria

Participants who meet the following criteria will be included:
▪ Meet the American College of Rheumatology criteria for FM in 1990 [16];▪ Age not less than 18 years old;▪ No acupuncture contraindications;▪ Informed consent obtained;▪ No FM medication or stop FM medication for at least 2 weeks.

#### Exclusion criteria

Subjects who fulfill any of the following criteria will be excluded:
▪ Subjects with severe systemic disorders (lymphoma; central nervous system, renal, or pulmonary involvement; myositis or vasculitis), renal or liver failure;▪ Subjects with systemic or local acute infection;▪ Subjects with complications of other rheumatic diseases;▪ Subjects with the pain visual analog scale score less than 4.0 cm/10 cm;▪ Pregnant women;▪ Currently lactating women;▪ Women planning to become pregnant during the study period;▪ Subjects currently participating or having participated in another trial during the last 30 days prior to the initial screening examination;▪ Subjects having received acupuncture treatment.

### Participant recruitment

This randomized, sham-controlled, patient and assessor blinded trial will be conducted in Guang’anmen Hospital and Shenzhen Traditional Chinese Medicine Hospital, which will provide outpatient service for FM. Participants in this study will be recruited from either outpatient clinic or inpatient department via advertisement at hospital-based electronic social media platform and poster distribution in the public areas of hospitals and nearby communities with the details of this study and contact information.

The interested subjects will be advised to contact the research assistants by phone or on site for initial screening. The potential participant is registered and given an appointment with the assigned physician for checking the inclusion and exclusion criteria. Patients who meet all inclusion criteria but no exclusion criteria will be invited to participate in the study and provided with the details of this RCT. All the participants will be asked to sign an informed consent form with their comprehensive information collected. The participants will be randomly assigned into two groups: the acupuncture group and the sham acupuncture group. All patients will not be informed about which group they have been assigned to in order to maintain blinding in this trial. Then, the baseline assessments will be performed by the same physician and recorded in CRF. All participants will undergo 8-week treatment and 16-week follow-up with relevant assessments every month in CRF. Each participant will be given a schedule for the dates of intervention and follow-up appointments performed by a research assistant who is neither involved in the treatment nor in the randomization.

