### Randomization and blinding

The study is a two-center, double-blind, and placebo-controlled trial. With the block randomization method, the random number table will be generated by an independent third party, the Hospital’s Clinical Evaluation Center, using SAS 9.4 software (SAS Institute, Cary, NC, USA). The randomized assignment sequence is placed in a sealed opaque envelope whereas the blind codes are kept at the department of research management and can be reproduced when needed. All of the patients participated in this study; principal investigators and research staff will remain blinded to all patients’ randomization assignments throughout the duration of this study. Eligible patients will be randomly allocated to either the acupuncture or sham group according to a 1:1 ratio.

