### Process of the treatment

Each participant will be interviewed by an investigator prior to the commence of treatment and fill out the CRF with a series of initial data at baseline of the study. After skin sterilization, an adhesive pad made of aseptic cylindrical polyethylene foam with double-sided tape on the bottom is placed on the acupuncture points for fixing the needle and implementation of blinding. The points and manipulation of acupuncture in both groups are the same, with Baihui (DU20), bilateral Tianzhu (BL10), bilateral Jianjing (GB21), bilateral Quyuan (SI13), bilateral Shousanli (LI10), Ququan (LR8), and bilateral Taichong (LR3) with even method, bilateral Sanyinjiao (SP6), Zusanli (ST36) with reinforcing method (Fig. 2). Needles will be retained for 30 min during treatment. Following needle insertion, the state of “de qi” (feelings of patients including soreness, numbness, heaviness, or tingle at the points) is achieved by twirling, lifting, and thrusting, which is essential for the effective treatment [17].

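### Baseline assessments are described after random assignment, though before treatment; completing them before the envelope is opened is a free, minor improvement

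*Protocol article*

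**What the plan says.** The Participant recruitment section of the protocol article tells the story in order: screening, eligibility check by an assigned physician, consent, and then "The participants will be randomly assigned into two groups: the acupuncture group and the sham acupuncture group". Next comes a sentence on blinding, "All patients will not be informed about which group they have been assigned to in order to maintain blinding in this trial", followed by "Then, the baseline assessments will be performed by the same physician and recorded in CRF".

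Two other sections place baseline relative to treatment, but not relative to randomisation. Process of the treatment says "Each participant will be interviewed by an investigator prior to the commence of treatment and fill out the CRF". Primary outcomes says of the FIQR: "Each subject will be asked to complete the questionnaire before treatment based on the overall situation of the past 24 h".

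On blinding, Participant recruitment opens with "This randomized, sham-controlled, patient and assessor blinded trial will be conducted in" the two hospitals, and Randomization and blinding adds that "principal investigators and research staff will remain blinded to all patients’ randomization assignments throughout the duration of this study". The Discussion keeps acupuncturists out of the interviews and has other investigators collect the clinical data in a different room.

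Baseline matters to the planned comparison. Under Sample size, "The calculation for sample size was based on the changes in pain VAS scores", and under Secondary outcomes the tender-point count is compared with its baseline value. Statistical analysis specifies intention to treat.

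**The concern.** A baseline is normally fixed before allocation so that it cannot depend on it. Here the allocation already exists when the baseline is taken. Two things follow.

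- **Possible influence.** The FIQR and most of the secondary scales are subjective self-reports, and the tender-point count depends on pressure applied by an assessor. If the allocation became known to the patient or the assessor before baseline, these values could shift between arms. In an unadjusted change score such a shift would pass straight into the estimated effect.
- **Missing baselines.** A patient who leaves after assignment but before baseline belongs to the intention-to-treat population, yet has no described baseline FIQR, tender-point count or secondary scale. The FIQR is one of the two listed primary outcomes.

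The article gives no reason for taking baseline after assignment.

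**Working it through.** **1. The order, section by section (protocol article)**

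| Section | Baseline relative to randomisation | Baseline relative to treatment |
|---|---|---|
| Participant recruitment | After | Described before the 8-week treatment |
| Process of the treatment | Not stated | Before |
| Primary outcomes (FIQR) | Not stated | Before |

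The three sections agree with each other: baseline falls between assignment and the first session. No text shown places it before assignment. The trial flow and SPIRIT figures are not visible here and may show a different order.

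**2. Which measures have a pre-allocation value**

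The exclusion criteria rule out a pain VAS below 4.0 on a 10 cm scale, so a pain VAS must be taken at the eligibility check, before assignment. Nothing says that this value is the baseline. No pre-allocation FIQR, MAF, SF-36, BDI, PSQI or pss-14 is described. Nor is a pre-allocation tender-point count identified as the baseline.

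**3. The plan's own sample size**

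Inputs from Sample size: difference 1.5, SDs 2.55 and 1.25, two-sided α 0.05, power 0.80, 1:1 allocation, about 15% dropout, 68 in total.

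- Average variance = (2.55² + 1.25²)/2 = (6.5025 + 1.5625)/2 = 4.0325, so SD = 2.008.
- n per group = 2 × (1.960 + 0.842)² × 4.0325 / 1.5² ≈ 28.1, rounded up to 29. The stated 29 is reproduced.
- With 34 per arm and 15% dropout, 34 × 0.85 = 28.9 per arm remain.

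**4. Cost in power of losing patients between assignment and baseline**

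The article gives no rate for this loss, so a range is assumed. Patients per arm with a change score = 28.9 × (1 − loss). Power is the normal approximation at difference 1.5 and SD 2.008.

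| Assumed loss | Per arm | Power |
|---|---|---|
| 0% | 28.9 | 0.810 |
| 1% | 28.6 | 0.807 |
| 3% | 28.0 | 0.799 |
| 5% | 27.5 | 0.790 |
| 10% | 26.0 | 0.768 |

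This treats the VAS change as unavailable for such patients, which is the worst case given that a screening VAS must exist. A Welch t calculation runs about 0.02 lower throughout (0.792 at 0%, 0.746 at 10%).

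**5. Purely hypothetical sensitivity to a baseline shift**

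For an unadjusted change score with 29 per arm, SE = √((2.55² + 1.25²)/29) = √(8.065/29) = 0.527. If there were no treatment effect and mean baseline VAS differed between arms by an invented 0.1, 0.3 or 0.6 cm, the two-sided rejection rate (noncentral t, 56 df) would be 5.4%, 8.7% or 20.1%. Nothing in the article makes any of these shifts plausible under the stated blinding, and Statistical analysis does not name a change-score test for the primary outcome. The figures show sensitivity only and are not used in the conclusion.

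**The case against.** The strongest reply is that the article declares the very protections that would prevent harm. Patients are not told their group, assessors and research staff are blinded, the sequence is in a sealed envelope, and acupuncturists do not collect data. At baseline no needle has yet been used, so the patient has had no treatment experience from which to guess. If the allocation did leak that early, every later assessment would suffer too, and visit order would be the lesser problem. The order also rests on one connecting word in a condensed article whose schedule figures are not visible here.

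Most of this stands, and it limits the point. A reader might infer that the baseline is in fact exposed to knowledge of allocation. The documents do not support that, because nowhere do they say that the patient or the baseline physician knows the group. A reader might also infer that patients lost in between have no baseline at all. For pain VAS that is too strong, because a screening value must exist. Nor can a one-for-one bias in a primary change score be claimed: the change score comes from Sample size, whereas Statistical analysis names a chi-square or Fisher's exact test for the primary outcome.

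The objection does not remove the stated sequence. Blinding here relies on people who can see whether a needle is blunt or sharp keeping that information to themselves. A baseline recorded before allocation needs no such reliance. The gap for withdrawn patients does not depend on blinding at all.

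**Conclusion.** The point holds as a minor matter of order. The article places baseline after random assignment and before treatment, and no bias is demonstrated. What remains is an avoidable route for influence on FIQR, tender points and the secondary scales should concealment or blinding fail, and a possible absence of baseline on those measures for some intention-to-treat patients. On power the effect is small: up to 5% loss in the interval costs about 0.02 (0.810 to 0.790), and only a loss near 10% costs about 0.04. Those loss rates are assumptions. The conclusion also assumes that the figures not shown do not give a different order; if they do, the Participant recruitment text still needs to be brought into line.

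**What to change.** Reorder the steps in Participant recruitment and in the SOP: consent, eligibility check, full baseline assessment recorded in the CRF, then opening of the envelope. The physician who checks eligibility is evidently also the one who takes the baseline, so both can be done before allocation. State whether the screening pain VAS or a separate measurement serves as the baseline VAS.

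Recruitment began in July 2018, so for patients already enrolled compare the baseline and randomisation dates and report, by arm, how many baselines were recorded after allocation and how many patients withdrew in between. If practice already followed the recommended order, a one-sentence correction of the text is enough.

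The cost is a change in the order of steps and a check of dates already on record. No extra visit or staff is needed, and the sample size of 29 per group and 68 in total does not change.
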